## Outcome measures

### Primary outcome

#### Help-seeking behaviour

Changes in help-seeking behaviour will be assessed by determining if participants sought mental health treatment within one month after attending the FCHVs intervention. Mental health treatment is defined as treatment provided by health care providers including trained primary health care workers, doctors, and mental health specialists. This does not include treatment provided by traditional healers and religious leaders. Research assistants, who are unaware of the participants’ assignment to the intervention, will visit their homes one month post-intervention. They will inquire about the participants’ interactions with FCHVs, the places/providers they visited for seeking care, and the reasons for choosing a specific provider using a semi-structured questionnaire. We will not verify the accuracy of the treatment they received. Participants who did not seek treatment will also be asked about the reasons for not seeking care and their plans to seek treatment soon. Participants will be asked a “yes” or “no” question: “Did you seek help for your health issue after attending the FCHV session?” with a yes or no response. We will report the percentage of participants who respond “yes” to this question as an indicator of seeking treatment.

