## Methods

### Objective

The aim of this study is to analyze the active components of Gain-Life (Give informAtIoN to transform Life), a community-based intervention designed to promote help-seeking for depression care. The study will examine the effects of intervention components including information on depression, awareness of treatment options, stigma reduction, dispelling myths about depression, and sharing personal transformation experiences, on help-seeking behaviour as the primary outcome and treatment adherence as secondary outcomes. Furthermore, the study will evaluate the delivery methods and assess the feasibility, acceptability, and appropriateness of Gain-Life intervention in encouraging help-seeking for depression care.

The primary research question of this study is to determine which component of the Gain-Life intervention has a positive impact on the primary outcome of help-seeking behaviour among individuals with depression. This outcome is measured as the percentage of people seeking care from a health care provider within one month of receiving the intervention.The secondary research question aims to evaluate the intervention’s effects on different outcomes, such as treatment adherence, reduction in depression symptom severity, and the feasibility, acceptability, and appropriateness of Gain-Life in promoting help-seeking for depression treatment.

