### Implementation process of Gain Life intervention

FCHVs will utilize the CIDT in their daily tasks to identify individuals experiencing depression. They will initially consider individuals whose experiences resonate with the CIDT vignette. Upon identifying a potential candidate, FCHVs will engage in a consultation to evaluate the impact of the issue on the individual’s daily life and their readiness to seek assistance. If the individual agrees to participate in the Gain Life intervention, FCHVs will arrange a suitable date and time for its implementation.

As per the study protocol, participants may receive all four components of the Gain Life intervention or a combination of three, two, or one component. FCHVs will coordinate the intervention implementation accordingly, with a maximum of two components being delivered simultaneously. In cases where three components are required, they will be administered on separate days. The intervention sessions will take place in confidential settings, such as the participant’s or FCHV’s residence, to ensure privacy. While family members are encouraged to join, participants who prefer not to involve them can opt for individual sessions.

Participants may choose not to receive all allocated components of the intervention for reasons such as feeling that they do not need the additional components, starting treatment after receiving initial components, or other contextual factors. These participants will still be included in the analysis using an intention-to-treat approach. Additionally, there will be no restrictions on participants receiving other interventions, support, or attending awareness programmes. These aspects will be explored in the qualitative component of the intervention.

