### Primary outcome

As recommended for factorial designs, effect coding will be utilized for all analyses [13]. The primary outcome of interest is change in help-seeking behaviour. This will be evaluated by determining the proportion of participants who attended the Gain Life intervention and sought care from health care providers rather than traditional or religious leaders. This will be measured by the number of participants who received the Gain Life intervention and sought treatment from health care providers. General linear regression models will be used to test the main effects of the Gain Life intervention components and their association with the primary outcome of interest [52].

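### The primary outcome's month has no defined starting session, so follow-up can depend on allocation, and the endpoint wording omits randomised people who attend no session

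*Protocol article*

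**What the plan says.** All references are to the protocol article.

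- **Window.** The Objective section defines the outcome as the "percentage of people seeking care from a health care provider within one month of receiving the intervention". The Help-seeking behaviour section assesses it by "determining if participants sought mental health treatment within one month after attending the FCHVs intervention".
- **Visit and scored item.** Research assistants "will visit their homes one month post-intervention". The reported result is the percentage answering yes to "Did you seek help for your health issue after attending the FCHV session". That item names one session and sets no time limit.
- **Delivery.** The Implementation process section allows at most two components at a time and adds: "In cases where three components are required, they will be administered on separate days". It gives neither the number of sessions nor the interval between them.
- **Partial receipt.** The same section foresees participants declining later components, one reason being "starting treatment after receiving initial components". Of those who do not take everything it says: "These participants will still be included in the analysis using an intention-to-treat approach". The Quantitative data analysis section repeats the intention-to-treat commitment.
- **Endpoint in the analysis.** The Primary outcome paragraph of the analysis section says: "This will be measured by the number of participants who received the Gain Life intervention and sought treatment from health care providers".

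**The concern.** Attending, receiving and post-intervention all describe events after randomisation, and their timing depends on delivery. The number of delivery days depends on the condition. If the interview falls one month after the intervention is completed, a multi-session participant is seen later after the first session than a single-session participant. Whether the extra days add or remove successes depends on how that participant reads a question about the session, in the singular.

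This would not average out in the factorial. Every candidate component, when on, moves participants towards multi-session conditions. A timing artefact would therefore look like a benefit, or a harm, of all three components at once, and the trial exists to choose between components.

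The second matter is the analysis set. Under the Recruitment and Randomization sections, allocation comes before delivery, so some people may be randomised and never attend. They have no starting date for the month, and the analysis wording does not count them.

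**Working it through.** **1. The plan's own figures.** The Sample sizes section gives 40% against 60%, 90% power, alpha 0.05 and 288 in total, which is 144 on against 144 off per factor. Two-sided, without continuity correction: n = (1.960·√(2·0.5·0.5) + 1.282·√(0.4·0.6 + 0.6·0.4))² / 0.2² = 129.3, so 130 per level and 260 in total. With continuity correction it is 140 per level and 280 in total, within 3% of 288. Power at 144 per level is 0.928. The sample size is therefore not at issue; I use only the 40%, the planned 20-point difference and the 144 per level.

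**2. Which conditions need more than one day.** From Table 1, condition 8 has one component; 4, 6 and 7 have two; 2, 3 and 5 have three; 1 has four. With at most two together, conditions 1, 2, 3 and 5 need at least two days.

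**3. Spread across factor levels.** For each factor, the four on conditions have 4, 3, 3 and 2 components and the four off conditions have 3, 2, 2 and 1. Multi-session share: on 3 × 36 = 108 of 144 (75%); off 1 × 36 = 36 of 144 (25%). Half of any multi-session excess passes into each main effect.

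**4. Reading A: visit 30 days after the last session, help counted from the first.** Assumptions: no component effect; constant hazard giving 40% in 30 days, so P(t) = 1 − 0.6^(t/30); two sessions, g days apart. Spurious effect = (0.75 − 0.25) × [P(30 + g) − 0.40]. Type I error is the normal-approximation rejection probability of a two-sided 5% test with 144 per level.

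| Gap g (days) | P(30 + g) | Spurious main effect | Actual type I error |
|---|---|---|---|
| 1 | 41.0% | +0.5 points | about 5.1% |
| 3 | 43.0% | +1.5 points | about 5.8% |
| 7 | 46.7% | +3.4 points | about 8.9% |
| 14 | 52.7% | +6.4 points | about 19.1% |

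If three- and four-component conditions instead take three sessions, the same gaps give +1.0, +2.9, +6.4 and +11.4 points.

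**5. Reading B: only help sought after the last session counts.** Counted rate in multi-session conditions = 0.40 × 0.6^(g/30). At g = 7, 11.2% have already sought help in the gap and the rate is 35.5%. The main effect is then 0.5 × (35.5 − 40) ≈ −2.2 points.

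**6. Reading C: question and visit both run from the first session.** Follow-up is 30 days in every condition and the artefact is zero.

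**7. Analysis set.** Three groups need a place:
- Full attenders are covered by both the intention-to-treat statements and the endpoint wording.
- Partial attenders are also covered: they attended, and two sections expressly keep them.
- Randomised people who attend nothing fall under an intention-to-treat model but outside the endpoint wording, and have no date from which to time the visit.

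The documents give no non-attendance rate. If it were 5%, 10% or 20%, an attenders-only analysis would leave about 136, 129 or 115 per level, with power of 0.914, 0.899 or 0.863. The loss of precision is modest; the main problem is selection after randomisation.

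**The case against.** The strongest reply is that no section says the month runs from the last session. The nominal window is one month in every condition, and the question's reference to a single session is compatible with a first-session start, under which follow-up is equal. A reader might infer that the protocol prescribes unequal follow-up; it does not. This part of the reply stands: what can be shown is an undefined anchor. It does not remove the point, because timing a visit post-intervention most naturally means after completion, and an item without a time limit cannot restore equal windows.

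The schedule figure is not shown, and the full protocol may fix visit timing or session spacing. That limits how firmly anyone can say what will happen in the field. The article nonetheless states the outcome definition in three places, and none names the session.

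The size rests on assumed gaps. Separate days may be consecutive, and gaps of 1 to 3 days give only 0.5 to 1.5 points against a planned 20. This stands, and the sign is also open.

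A reader might also infer a general breach of intention-to-treat. The documents do not support that, since partial attenders are expressly retained. The analysis paragraph could be a loose description and not a denominator rule. Even so, it conflicts with the intention-to-treat model for never-attenders, whose number is unknown.

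Finally, the choice of time zero depends partly on the estimand. Counting from randomisation gives multi-session participants less time after full delivery. This is a real trade-off, though a common clock keeps the randomised comparison intact.

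**Conclusion.** The point holds in a limited form. The primary outcome is timed from an event after randomisation whose defining session is not stated, and the scored item has no time limit. Followed as written, the protocol permits follow-up that depends on allocation, with an artefact of the same sign in all three main effects. Under a constant hazard of 40% in 30 days and two sessions, the artefact is negligible if sessions fall on consecutive days. It is no longer negligible at a week or more, and it turns negative if between-session help is not counted. Neither its size nor its sign can be fixed from the documents, and it vanishes under a first-session anchor.

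The conflict with intention-to-treat is real but confined to randomised people who attend no session. Both matters should be corrected; neither shows that the trial's results will be biased.

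**What to change.** 1. Set one time zero common to all eight conditions: randomisation, or the first session with the randomisation date as fallback for people who never attend.
2. Date the home visit and one fixed window to that time zero. A window stretched to cover the slowest delivery schedule is not needed.
3. Count any provider visit in the window that meets the protocol's own definition of mental health treatment, including visits between sessions, and record its date so that the window can be applied.
4. In the Objective, Help-seeking behaviour and analysis Primary outcome sections, define the endpoint over all randomised participants, in place of those who attended or received the intervention.
5. Keep one month after the last session as a sensitivity analysis.

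The cost is wording and visit scheduling, with no change in sample size. Time after full delivery becomes somewhat shorter in multi-session conditions. The Timeline section shows that delivery began in June and baseline data collection in July 2024, so visits already made cannot be re-dated. For those participants, the window should be applied to the reported dates of provider visits where available.

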### Sample sizes and sampling process

The sample size for this study was determined based on the need to detect a difference in help-seeking behaviour between participants receiving the mental health literacy component (i.e. information about depression) alone (40%) and those receiving both the mental health literacy and stigma, myths, and facts about depression components (60%) [32, 53]. With 90% power and a significance level of 0.05, a total sample size of 288 participants is required, with 36 participants per condition. This sample size will allow to determine which component of the Gain-Life intervention positively impacts the primary outcome of help-seeking behaviour among individuals with depression.

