### Blinding

Data collectors conducting baseline and follow-up interviews will remain blinded. The Principal Investigator (PI), trainers/supervisors, FCHVs, and participants will not be blinded to the treatment conditions. The PI, who is responsible for managing the study, randomizing participants, and supervising field activities including quality control, will not be blinded to the treatment condition. The statistician, who analyzes the quantitative data for the study, remains blinded (Fig. 1).

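### The primary outcome is an unblinded participant's 'yes' with no described check of an eligible visit, so extra over-reporting caused by one component enters its main effect

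*Protocol article*

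**What the plan says.** In the Protocol article, the Help-seeking behaviour section defines the outcome as mental health treatment from a health care provider within one month of the intervention, and excludes traditional healers and religious leaders. The measured item is one yes/no question, "Did you seek help for your health issue after attending the FCHV session", and the percentage answering 'yes' is the reported indicator. The question names neither the type of provider, nor mental health care, nor the one-month window.

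In the same interview, research assistants unaware of allocation also ask about "the places/providers they visited for seeking care, and the reasons for choosing a specific provider". The section adds: "We will not verify the accuracy of the treatment they received".

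The Blinding section states: "The Principal Investigator (PI), trainers/supervisors, FCHVs, and participants will not be blinded to the treatment conditions". Data collectors and the statistician are blinded.

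The analysis section on the primary outcome words it as care from health care providers as opposed to traditional or religious leaders, and says: "General linear regression models will be used to test the main effects of the Gain Life intervention components". The Discussion lists single-blinding as a limitation but does not mention self-report.

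**The concern.** Everything the article describes about whether a participant sought care comes from that participant, who knows what he or she was taught. The three candidate components bear on what a person may feel is the right answer. One describes specific services, their costs and opening hours. One explains that stigma hinders care seeking. One shows people who recovered through treatment. Each could raise the wish to answer 'yes' without an eligible visit behind it.

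If that happens more often when a component is on than when it is off, the difference is added to the component's estimated effect. Blinding the interviewer does not help, because the error arises in the answer and not in how it is recorded. At stake is the choice of components for a later full trial or a further optimization study. A component that moves reports but not visits could be carried forward.

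**Working it through.** **Inputs from the article**
- Design: "With 90% power and a significance level of 0.05, a total sample size of 288 participants is required, with 36 participants per condition" (Sample sizes and sampling process). Planning rates are 40% and 60%. Sidedness is not stated; two-sided is assumed.
- Table 1: each candidate component is on in four conditions and off in four, so a main effect compares 4 × 36 = 144 with 144.

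**The plan's own figure**
- Per level, n = [1.96·√(2·0.5·0.5) + 1.2816·√(0.4·0.6 + 0.6·0.4)]² / 0.20² = 129.3, rounded up to 130, or 260 in total.
- With continuity correction it is 140 per level, 280 in total, which is within 3% of 288.
- Power at 144 v 144 is 92.8% (pooled variance) or 93.4% (unpooled). The stated size is therefore consistent with a main-effect comparison.

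**Model for over-reporting.** Let t be the true proportion seeking care and f the proportion of true non-seekers who answer 'yes'. The observed proportion is t + (1 − t)·f. The article gives no f, so the values below are assumptions shown as a range.

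**No true effect, t = 0.40 at both levels.** Two-sided 5% z-test, unpooled, SE = √[p₁(1−p₁)/144 + p₂(1−p₂)/144].

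| f off v on | Observed off v on | Spurious difference | SE | Chance of p < 0.05 |
|---|---|---|---|---|
| 5% v 5% | 43% v 43% | 0 | 0.058 | 5.0% |
| 5% v 10% | 43% v 46% | 3 points | 0.058 | 8.1% |
| 5% v 15% | 43% v 49% | 6 points | 0.059 | 17.6% |
| 5% v 20% | 43% v 52% | 9 points | 0.059 | 33.6% |

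For example, 0.40 + 0.60·0.15 = 0.49. A pooled test gives nearly the same results (8.0%, 17.5%, 33.3%).

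**Equal over-reporting, true 40% v 60%, f = 10% at both levels.** Observed rates are 0.40 + 0.60·0.10 = 46% and 0.60 + 0.40·0.10 = 64%. The 20-point effect shrinks to 18, and power falls from 93.4% to 87.7% (unpooled).

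**A documented-visit count used as the test.** Assume half of true visits leave no document. A true 40% v 60% then becomes 20% v 30%, SE = 0.051, and power is about 50%.

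**The case against.** The strongest reply is that the design already limits this bias.
- Every participant, including those in the information-only condition, is told in person about the consequences of untreated depression.
- Randomization is within each Female Community Health Volunteer (FCHV), so the wish to please her is much the same across conditions.
- What is common to both levels creates no false effect. Only the increment from one added component does, and at 5% v 10% the error rate is barely above nominal.
- A false 'yes' must also survive questions about where the person went and why. Those who started treatment are asked at three months whether they are still with the same provider.

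All of this stands and limits the likely size. It does not remove the problem, because every one of these checks is also self-report and the stated indicator remains the bare 'yes'.

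A reader might take "We will not verify the accuracy of the treatment they received" as an admission that visits will not be verified. The wording does not support that: it speaks of the treatment received. What can be said is that the article describes no check of the visit anywhere. A reader might also infer that the yes/no answer is the only information on care seeking. It is not, since the provider visited is already asked.

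Finally, self-report is a practical choice that the article states openly, and a component wrongly kept may face another test in a later trial. That bears on severity, not on whether a supporting analysis is worthwhile.

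**Conclusion.** The concern holds as a risk of bias in the component main effects, not as a demonstrated error. The text establishes three things: participants are unblinded, the outcome is scored on an unchecked 'yes', and the question is looser than the definition it is meant to measure. How far over-reporting differs by component is unknown. Over the assumed range, the false-positive rate for a component runs from about 8% to about 34% against a nominal 5%. Equal over-reporting only costs power, about 6 points at a 10% rate. These figures assume 40% true help-seeking, 144 v 144 with complete follow-up, a two-sided test and no false 'no' answers.

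The documents do not support saying that a component will be falsely declared active, only that the primary outcome as scored could not tell such a component from a truly active one. A modest addition to the planned interview and analysis is warranted.

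**What to change.** 1. Keep the self-reported 'yes' as the primary outcome.
2. In the planned one-month interview, for each 'yes', record the provider already asked about, the date of the visit, and whether a visit slip, prescription or dispensed medicine was seen or not seen.
3. Pre-specify two supporting re-runs of the same component model:
   - (a) counting only 'yes' answers with a named eligible provider within one month. This also brings the item into line with the outcome as defined under Help-seeking behaviour and as worded in the analysis section;
   - (b) counting only those for whom a document was also seen.
4. Report both as sensitivity analyses. Do not make them a condition for calling a component active: if half of true visits leave no document, run (b) has only about 50% power for the planned effect. If they disagree with the primary analysis, describe the primary result as an effect on reported help-seeking.
5. Keep the sentence on verification, since deleting it would verify nothing, but state whether it refers to the visit or to the treatment given.

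The cost is a visit date, a seen/not-seen field and a short addition to an interview already planned, plus two repeats of one model. The downside is that the documented count will be lower and incomplete. Slips get lost, telephone interviews cannot show them, and interviews already completed will lack the new fields, since the Timeline puts the start of the intervention in June and of baseline data collection in July 2024.
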